#### Postoperative pain control

All primary and secondary outcome data of this trial are fully collected during the PACU stay. Therefore, no standardized postoperative analgesia protocol is enforced after PACU discharge, and no additional data will be collected beyond the PACU period.

Postoperative analgesia after PACU discharge is implemented entirely according to the patient’s autonomous preference. Patients may choose either intravenous patient-controlled analgesia (PCA) or on-demand bolus analgesia administered on the ward. The specific medication for on-demand bolus analgesia is determined by the attending on-duty physician based on clinical practice guidelines and individual patient conditions.

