### Status and timeline

*Participant recruitment*: Recruitment of eligible participants is scheduled to initiate on January 1, 2026, and is anticipated to be completed by December 31, 2026, at the Department of Anesthesiology, Ningbo No.6 Hospital.

*Data collection*: Perioperative baseline data, intervention-related data, and primary and secondary outcome data collection will be conducted concurrently with participant enrollment, and is expected to be fully completed by December 31, 2026. Data quality verification and cross-check will be performed synchronously during the collection period to ensure the integrity and accuracy of the dataset.

*Data management and statistical analysis*: Data cleaning, database locking, and final quality audit will be completed from January 2027 to February 2027. Formal statistical analysis for the primary non-inferiority test and secondary outcome analysis will be conducted from February 2027 to June 2027, in strict accordance with the predefined statistical analysis plan.

*Results availability*: Preliminary analysis results will be available by June 2027. The final study results are expected to be fully reported and submitted for academic publication by December 2027, with the development and promotion of the standardized operation procedure initiated thereafter.

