##### Case report form (CRF) design and standardization

A standardized, study-specific eCRF is developed in the ResMan system in accordance with the study protocol, covering all data points required for the trial’s primary and secondary endpoints, with a unified coding standard and filling specification. The eCRF includes the following modules: subject screening and eligibility confirmation, written informed consent documentation, baseline demographic and clinical characteristics, baseline vital signs and pulmonary function/diaphragmatic excursion measurements, study intervention details, perioperative general anesthesia related data, intraoperative and postoperative analgesic drug consumption, postoperative primary and secondary outcome assessments, postoperative follow-up data, adverse events and serious adverse events recording, protocol deviations, and subject withdrawal or loss to follow-up documentation.

Prior to the formal initiation of the trial, the eCRF is pre-tested and validated through the pre-trial data to ensure the rationality, comprehensiveness, and operability of the form. Version control is implemented for all eCRF modifications in the ResMan system, with any changes documented in writing and approved by the principal investigator and the data management team. All eCRFs are marked only with the subject’s unique study identification number (ID), with no information that may indicate the subject’s group allocation.

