##### Analysis of secondary outcomes

*Continuous variables*: Normally distributed data (e.g., diaphragmatic excursion, FEV1, FVC, emergence time, PACU stay duration) will be presented as mean ± standard deviation (SD), and between-group differences will be analyzed using the two-sample t-test. Non-normally distributed data (e.g., analgesic drug consumption, postoperative hospital length of stay) will be presented as median (interquartile range, IQR), and between-group differences will be analyzed using the Mann–Whitney U test.*Categorical variables*: Data will be presented as counts (percentages). Between-group comparisons will be performed using the chi-square (χ^2^) test for large sample sizes or Fisher’s exact test for cell counts < 5.*Ordinal variables* (e.g., sensory and motor block scores): Between-group differences will be analyzed using the Mann–Whitney U test.

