### Data monitoring committee

An independent Data Monitoring Committee (DMC) was established to monitor trial safety, data quality and feasibility, providing objective advisory opinions on trial continuation or termination. The DMC operates independently of the study sponsor and investigators with no conflicts of interest.

1 Composition

The DMC consists of 3 independent experts:

1 senior anesthesiologist specializing in regional anesthesia1 biostatistician with clinical trial experience1 clinical ethicist

All members sign a conflict-of-interest disclosure form before joining. Any new conflicts arising during the trial must be reported immediately.

2 Core responsibilities

*Safety monitoring*: Review all adverse events (AEs) and serious adverse events (SAEs), assess their causal relationship with the study intervention, and identify unexpected safety signals*Data quality supervision*: Evaluate data completeness, protocol compliance, and the integrity of blinding procedures*Feasibility assessment*: Monitor recruitment rates and dropout rates, provide recommendations for adjusting trial strategies if needed*Emergency decisions*: Recommend emergency unblinding only when essential for life-saving treatment, or recommend early trial termination if unacceptable safety risks are identified

3 Meeting and reporting

Regular meetings are held every 3 months during enrollment, with an interim meeting at 50% enrollment (50 subjects)Emergency meetings are convened within 24 h of notification of a serious adverse eventAll DMC recommendations are submitted in writing to the principal investigator and institutional ethics committee, with detailed meeting minutes archived for 5 years after trial completion

4 Confidentiality

All DMC members sign a confidentiality agreement. They only access de-identified, aggregated data labeled as “Group A” and “Group B” to maintain blinding. No trial data or discussions may be disclosed to third parties until the results are formally published.

Harms

All adverse events (AEs) occurring from the time of signing the informed consent form until the completion of the 3-day postoperative follow-up will be recorded and reported, regardless of their causal relationship with the study intervention.

5 Definition and classification

*Adverse events (AEs)*: Any unfavorable medical occurrence in a study subject, including but not limited to:

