Local anesthetic-related: Local anesthetic toxicity, allergic reaction, injection site pain, hematomaNerve-related: Transient paresthesia, persistent sensory or motor deficitRespiratory-related: Hoarseness, Horner syndrome, dyspnea, hypoxemiaGeneral: Nausea, vomiting, hypotension, bradycardia, postoperative dizziness

*Serious adverse events (SAEs)*: Any AE that results in death, life-threatening condition, permanent disability, prolonged hospitalization, or requires emergency medical intervention. For this trial, special attention will be paid to severe respiratory distress requiring non-invasive or invasive ventilation, and permanent neurological injury.

6 Causal relationship assessment

Each AE will be assessed for its causal relationship with the study intervention by the principal investigator, classified as definitely related, probably related, possibly related, probably unrelated, or definitely unrelated. Only AEs classified as definitely or probably related to the study intervention will be considered treatment-related.

7 Reporting and management

All AEs will be recorded in detail in the case report form (CRF), including onset time, severity, duration, treatment measures, and final outcome.All SAEs must be reported to the institutional ethics committee and the Data Monitoring Committee (DMC) within 24 h of occurrence. A written follow-up report will be submitted within 7 days with detailed information on the event and its management.Subjects experiencing any AE will receive appropriate medical treatment and close follow-up until the event resolves or stabilizes.

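### The protocol ends all data collection at PACU discharge, which contradicts its own 3-day adverse-event follow-up and its length-of-stay outcome

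*Protocol article*

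**What the plan says.** The cut-off is stated twice in the section Postoperative pain control. The first statement is "All primary and secondary outcome data of this trial are fully collected during the PACU stay". The second, given as a consequence, is that "no additional data will be collected beyond the PACU period".

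Other sections of the same article plan for data beyond that point:

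- The Harms text, under Data monitoring committee, opens the adverse-event window at consent and keeps it open: events "until the completion of the 3-day postoperative follow-up will be recorded and reported". It also promises any patient with an adverse event "close follow-up until the event resolves or stabilizes".
- Secondary outcomes lists length of hospital stay after surgery among the recovery indicators. It lists nerve injury and permanent neurological deficit among the safety indicators.
- Analysis of secondary outcomes names "postoperative hospital length of stay" among the variables to be shown as median and interquartile range and compared by the Mann–Whitney U test.
- The case report form section includes a module for "postoperative follow-up data, adverse events and serious adverse events recording", and the data entry section times entry after each patient's full follow-up.

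The Data collection section, which sets out what is gathered and when, has the PACU as its last timed block. It has no later contact and no length-of-stay item. Its safety item refers to perioperative adverse events without giving an end point.

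**The concern.** A protocol should give one answer to the question of when observation stops. This one gives two. Staff who work from the pain-control section and the collection list would stop at PACU discharge. Staff who work from the harms section would continue for three days and beyond for unresolved events.

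The safety tables and one secondary outcome are at stake. Nerve injury, permanent deficit and late breathing problems are listed as outcomes or as adverse events of interest, and some of them appear, or can be judged, only after the patient has left the PACU. If they are not looked for, a small number of events says something about the length of observation as well as about the two volumes. That matters in a trial that hopes to support a safer regimen.

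**Working it through.** No calculation applies to the contradiction. The check is a comparison of the sections, asking of each promised item whether it can be known at PACU discharge.

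1. **Scope of the cut-off.** The sentence stands under pain control, and its context is why analgesia is not standardized afterwards. Its wording, however, covers all primary and all secondary outcome data and then excludes any further data. It cannot be read as covering analgesia data only.

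2. **Co-primary endpoints.** The pain score is taken on regaining full consciousness, and hemidiaphragmatic paresis is assessed before PACU discharge. Both fit within the cut-off.

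3. **Functional, block and analgesic secondary outcomes.** Diaphragmatic excursion, FEV1, FVC, the sensory and motor scores, intraoperative sufentanil and PACU rescue sufentanil are all known by PACU discharge. They fit as well.

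4. **Hospital length of stay.** It has no value until the patient leaves hospital, so it cannot be collected under the cut-off. The complete-case rule that the plan sets for missing secondary outcomes does not help if nobody has a value.

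5. **Adverse events to day 3.** A window that ends three days after surgery cannot close at PACU discharge. Safety data are not imputed, so an event not observed is simply absent from the tables.

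6. **Nerve injury and permanent deficit.** The protocol schedules sensory and motor block scores of five nerves before PACU discharge, so it expects some deficit from the block itself at that time. I assume that an injury may not be separable from a working block then; the article gives no block duration to test this. Permanence cannot be established in the PACU. Three days would not establish it either, and this outcome depends on the promise to follow each event until it settles.

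7. **Adverse-event summaries.** The Safety analysis section summarizes duration and final outcome of every event. For an event still present at PACU discharge, both require later data.

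8. **Is there a reconciling sentence?** None is visible. The collection list sides with the cut-off by omission. The case report form module and the timing of data entry side with follow-up. The schedule figure is not shown. It might reveal the intended window, but it could not remove a conflict in the text.

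9. **Calendar (minor).** Status and timeline projects recruitment to end on December 31, 2026, and says that data collection "is expected to be fully completed by December 31, 2026". A 3-day window closes by that date only for surgery on or before December 28 (31 − 3 = 28). Consent is one day before surgery, so a patient recruited on the last day would have surgery on January 1, 2027.

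**The case against.** The strongest reply is that the offending sentence is a loose remark in a section about analgesia, and that the sections responsible for harms, the case report form and data entry all assume follow-up. Staff using the harms section would collect the late events. Serious adverse events must be reported within 24 hours of occurrence with no PACU limit, and every reported event enters the safety analysis. Length of stay can be read from the hospital record. Secondary outcomes are declared exploratory, and 50 patients per group could not support inference on permanent nerve injury in any case. The dates in the timeline are projections.

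Most of this stands, and it limits the consequence. A reader might infer that late harms and length of stay will certainly be lost. The documents do not support that, because loss follows only if the cut-off governs. A reader might also infer that nerve injury and respiratory events would be zero in both groups by construction. That goes too far: nausea, hypotension, hoarseness, Horner syndrome, dyspnea and other events visible in the PACU are recorded on either reading, persistent paresthesia during the block is documented at once, and late serious events have their own reporting route. Nor is length of stay irretrievable for all patients.

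The reply does not remove the contradiction. The cut-off is unqualified, the collection list agrees with it, and nothing tells staff which text to follow. A non-serious symptom not asked about on day 3 cannot be reliably recovered later.

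**Conclusion.** The point holds as an internal contradiction on the data-collection window. The PACU cut-off cannot be met together with the 3-day adverse-event window, the follow-up of ongoing events, or the length-of-stay outcome and its planned test.

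The consequence is conditional and confined. If the cut-off and the collection list are followed, length of stay is not collected as planned, and late respiratory events, nerve injury and permanent deficit may be under-recorded in both groups. A low count of these would then partly reflect when observation stopped. The documents give no rates for such events, so the size of the shortfall cannot be stated.

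The co-primary endpoints, the sample size and the success rule are not touched. The calendar issue is a side point, affecting only the last few patients under dates that are projections. The conclusion rests on the text alone, without the schedule figure. The one assumption, on separating nerve injury from a working block in the PACU, affects how much might be missed and not whether the sections conflict.

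**What to change.** Reconcile the sections so that one rule governs:

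- **Postoperative pain control:** limit the PACU cut-off to the co-primary outcomes and to the functional, block and analgesic secondary outcomes. State in the same place that adverse events are collected to the end of the 3-day follow-up, that ongoing events are followed as the harms text already requires, and that hospital length of stay is taken from the hospital record.
- **Data collection:** add a block after the PACU with these items, and give the perioperative adverse-event item the same end point as the harms text.
- **Status and timeline (minor):** set the end of data collection late enough to allow three days after the last patient's surgery. Cleaning and lock are planned for January to February 2027, so a shift of a few days should be absorbed.

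The cost is wording. No new outcome, test or patient is added, because the adverse-event window, the follow-up of events, the case report form module and the length-of-stay outcome are already in the plan. The article does not describe how the 3-day follow-up is carried out, so one line on who asks and how would make it workable. The change should be made before patients pass the point at which day-3 information can be obtained.

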### Data collection and management

All data collection and management processes of this trial are performed in strict accordance with the Good Clinical Practice (GCP) guidelines, the ethical principles of the Declaration of Helsinki, and the study protocol approved by the Ethics Committee of Ningbo NO.6 Hospital.

#### Data management

All study data are recorded, managed, and stored centrally via the Research Manager system (ResMan, http://www.medresman.org.cn), a web-based clinical trial management public platform certified by the Chinese Clinical Trial Registry, with complete functions for electronic case report form (eCRF) design, data entry, logical verification, audit trail, and database locking, fully complying with the regulatory requirements for clinical trial data management in China.

##### Data management governance and role allocation

An independent data management team consisting of two trained research assistants and one designated data manager is established for this trial. All members of the data management team have no involvement in the implementation of the study intervention, perioperative anesthesia management, baseline or postoperative outcome assessments, and randomization sequence generation, and remain fully blinded to the subject’s group allocation throughout the study. The specific responsibilities are clearly divided as follows:

The designated data manager is responsible for the overall design of the eCRF in the ResMan system, database establishment, hierarchical access control setting, and supervision of the entire data management process;The two independent research assistants are responsible for independent dual data entry, cross-verification, and discrepancy resolution in the ResMan system, with no communication with the study intervention anesthesiologist, outcome assessor, or study drug administrator regarding any content related to group allocation;[name], the dedicated anesthesiology nurse responsible for randomization sequence management and study drug preparation, is the only personnel with access to the complete randomization allocation list, and is prohibited from participating in any data management, data entry, or statistical analysis procedures. The randomization allocation list is stored in a separate encrypted module in the ResMan system, which will not be accessed by any personnel until the database is formally locked.

##### Case report form (CRF) design and standardization

A standardized, study-specific eCRF is developed in the ResMan system in accordance with the study protocol, covering all data points required for the trial’s primary and secondary endpoints, with a unified coding standard and filling specification. The eCRF includes the following modules: subject screening and eligibility confirmation, written informed consent documentation, baseline demographic and clinical characteristics, baseline vital signs and pulmonary function/diaphragmatic excursion measurements, study intervention details, perioperative general anesthesia related data, intraoperative and postoperative analgesic drug consumption, postoperative primary and secondary outcome assessments, postoperative follow-up data, adverse events and serious adverse events recording, protocol deviations, and subject withdrawal or loss to follow-up documentation.

Prior to the formal initiation of the trial, the eCRF is pre-tested and validated through the pre-trial data to ensure the rationality, comprehensiveness, and operability of the form. Version control is implemented for all eCRF modifications in the ResMan system, with any changes documented in writing and approved by the principal investigator and the data management team. All eCRFs are marked only with the subject’s unique study identification number (ID), with no information that may indicate the subject’s group allocation.

##### Data entry, verification, and discrepancy resolution

A dual independent data entry system is implemented in the ResMan system for all study data. After the completion of each subject’s full follow-up, the two independent research assistants enter the data from the original paper records and archived documents into the ResMan database separately, without any communication during the entry process. After dual entry is completed, the system automatically performs cross-verification to identify inconsistent data entries and generates a discrepancy report.

For any data discrepancies, missing values, or data that do not meet the pre-specified logical rules, the data management team generates a data query form in the ResMan system. The query form is sent to the corresponding investigator for source data verification and correction, with all query processes, correction content, and supporting documents fully documented and archived in the system. Source data verification (SDV) is performed for 100% of the co-primary endpoint data (incidence of hemidiaphragmatic paralysis and PACU resting NRS pain score), and no less than 30% of secondary endpoint data, baseline data, and adverse event data, to ensure that the data in the ResMan database is completely consistent with the original medical records, anesthesia record system, ultrasound image archives, and follow-up records.

##### Database access control and lock procedure

Strict hierarchical access control is set for the ResMan database: only the designated data manager has full administrative access to the database, the two research assistants only have data entry access without modification or deletion permissions, and all other study personnel have no access to the database. The system automatically generates an immutable audit trail for all operations in the database, recording the operator, operation time, details of data entry/modification/deletion (including pre-modification and post-modification values plus reasons for changes), and permission changes, to ensure full traceability of all data operations.

After all subjects have completed the study procedures, all data entry, verification, discrepancy resolution, and SDV are fully completed, and no further data updates, corrections, or additions are expected, the database will be formally locked in a blind state in the ResMan system. The database lock procedure is jointly completed by the principal investigator, data manager, independent statistician, and ethics committee representative. A written database lock record is signed and archived by all relevant personnel. Once the database is locked, no modifications to the data are allowed, except for the correction of critical data errors identified after unblinding, which requires a written application, detailed explanation of the reasons, and approval from the institutional ethics committee, with all correction processes fully documented and traceable. Formal unblinding and statistical analysis will only be performed after the database is completely locked.

